## Abstract

**Background:**

Poststroke depression is closely related to increased mortality in stroke patients. Compared with antidepressants, electroacupuncture (EA) treatment for poststroke depression (PSD) has relatively more stable effectiveness and can reduce side effects. This trial is designed to provide solid evidence for the efficacy and safety of EA treatment for patients with PSD.

**Methods/design:**

This ongoing study is a single-blind, single-center, parallel group, randomized controlled trial. Sixty-two participants will be recruited from Shanghai Shuguang Hospital and randomized into either the EA group or the sham EA group. Baihui, Sishencong, Ganshu, Sanyinjiao, and Taichong are selected as the treatment acupoints in both groups. The EA group will receive the traditional EA treatment with de-qi sensation, and the sham EA group will receive sham EA treatment without needle penetration and electrostimulation. Participants will receive treatment 3 times per week for a total of 12 sessions over 4 weeks. The primary outcome is Hamilton Rating Scale for Depression score, and the secondary outcomes are scores on the Zung Self-Rating Depression Scale, National Institutes of Health Stroke Scale, Barthel Index of Activities of Daily Living, and Depression Scale of traditional Chinese medicine. All of the outcome measures will be assessed at baseline, 2 weeks after EA treatment onset, 4 weeks after treatment onset, and at 8-week follow-up. Safety assessments will be done at each visit.

**Discussion:**

The results of this trial will demonstrate the efficacy and safety of EA treatment for PSD with credible and important clinical evidence, thus supporting EA treatment as an ideal choice for PSD treatment.

**Trial registration:**

Chinese Clinical Trial Registry, ChiCTR-IOR-17012610. Registered on 7 September 2017. http://www.chictr.org.cn/edit.aspx?pid=21494&htm=4

**Electronic supplementary material:**

The online version of this article (10.1186/s13063-018-2548-0) contains supplementary material, which is available to authorized users.

## Background

Stroke, a cardiovascular disorder with relatively high mortality, is a leading cause of serious long-term disability [1]. Researchers have shown that several neuropsychiatric problems, including depression, anxiety, dementia, apathy, and psychosis, may occur after stroke. Statistically, symptoms of depression occur in one-third of stroke survivors [2]. Thus, poststroke depression (PSD) is the most frequent neuropsychiatric sequela of stroke. PSD, whose major symptoms are melancholia and dysphoria, does harm to cognitive function, social activity, and stroke rehabilitation, which is closely related to the increase of mortality [3].

In the treatment of PSD, antidepressants such as citalopram, escitalopram, nortriptyline, milnacipran, mirtazapine, piracetam, and fluoxetine are most commonly used by Western doctors nowadays. However, it has been widely verified that the use of antidepressants in patients with PSD has an increased risk of adverse events (AEs) that may lead to other problems, including blurry vision, urinary retention, hypotension, sexual dysfunction, tremor, and severe insomnia [4]. Psychotherapy interventions, including cognitive behavioral therapy [5], a social work intervention using problem solving [6], advice on services and counseling, motivational interviewing [7], and a supportive intervention [8], have been demonstrated to be effective for the treatment of PSD [4], but currently the literature regarding the efficacy of psychological therapy for PSD is limited. The use of electroconvulsive therapy (ECT), involving the electrical induction of seizures in patients, is an effective protocol for treatment of PSD [9]. Nevertheless, some severe side effects of ECT, such as confusion, headache, nausea [10], mania, cognitive dysfunction, prolonged seizures, prolonged apnea, hypertension, and arrhythmia [11], have also been reported.

Acupuncture, a traditional Chinese therapy using needles to puncture into acupoints on the body surface, is based on the theory of meridians and the balance of yin, yang, qi, and blood [12, 13]. Currently, a number of clinical reports have demonstrated that electroacupuncture (EA) treatment for PSD is significantly effective with few side effects, but there are few randomized controlled trials (RCTs) showing this [14, 15]. Hence, lack of standard clinical RCTs results in insufficient evidence to support EA treatment for PSD. It is necessary to design a high-quality clinical RCT for PSD treated by EA. Our proposed trial will be conducted as a parallel group RCT to comprehensively evaluate the efficacy and safety of EA treatment for PSD by comparing an EA group with a sham EA group.

## Methods/design

### Hypotheses

Patients with PSD with 12 sessions (4 weeks) of EA treatment will have certain improvements in their symptoms and QoL scores.Patients with PSD treated with EA will experience alleviation of their symptoms and have increased QoL scores significantly greater than those treated by sham EA.

### Study design

We plan to conduct a single-center, patient-blinded, assessor-blinded, parallel group RCT strictly in accordance with the Consolidated Standards of Reporting Trials (CONSORT) [16] and STandards for Reporting Interventions in Clinical Trials of Acupuncture (STRICTA) guidelines [17]. The study will be conducted from October 2017 to October 2019 at Shuguang Hospital, affiliated with Shanghai University of Traditional Chinese Medicine in Shanghai, China. Figure 1 shows the planned flowchart of the trial. Figure 2 demonstrates the study schedule for enrollment, treatments, outcome measurements, and data collection. Additional file 1 contains the Standard Protocol Items: Recommendations for Interventional Trials (SPIRIT) checklist.

**Fig. 1 Fig1:**
[figure not shown]
The planned flowchart of the trial. *BI* Barthel Index of Activities of Daily Living, *EA* Electroacupuncture, *HRSD* Hamilton Rating Scale for Depression, *NIHSS* National Institutes of Health Stroke Scale, *SDS* Zung Self-Rating Depression Scale, *TCM* Traditional Chinese medicine

**Fig. 2 Fig2:**
[figure not shown]
The study schedule for enrollment, treatments, outcome measurements and data collection. *EA* Electroacupuncture, *HRSD* Hamilton Rating Scale for Depression, *SDS* Zung Self-Rating Depression Scale, *NIHSS* National Institutes of Health Stroke Scale, *BI* Barthel Index of Activities of Daily Living, *TCM* Traditional Chinese medicine

### Participants

#### Patient screening

The following patient screening will be done to conduct a safety assessment of patients and exclude patients with fatal conditions such as coma, complete paralysis, secondary intracerebral hemorrhage, and severe infections resulting from stroke:History inquiry and recordingPhysical examination, including muscle strength test, physiological reflex, pathological reflex, and Brunnstrom movement function assessment and coordination movement assessmentLaboratory tests, including complete blood count, C-reactive protein, and urinalysisBrain computed tomography

#### Inclusion criteria

Patients aged 40–85 years with no sex restrictionPatients who meet the diagnostic criteria of the guidelines for the diagnosis and treatment of patients with acute ischemic stroke [18] and the diagnostic criteria of insomnia according to the *Diagnostic and Statistical Manual of Mental Disorders, Fifth Edition* [19]Patients whose depression symptoms occur after stroke and whose Hamilton Rating Scale for Depression (HRSD) scores are between 8 and 35Patients willing to participate in the RCT and sign informed consent forms

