##### Hamilton Rating Scale for Depression

The HRSD, originally published by Max Hamilton [24], is a multiple-item questionnaire that can provide an indication of depression and act as a guide for evaluating recovery. It is designed to assess depression severity by probing mood, feelings of guilt, suicidal ideation, insomnia, agitation or retardation, anxiety, weight loss, and somatic symptoms. The participants will be rated along 24 dimensions with scoring on a 3- or 5-point scale. A score of 0–7 is considered to be normal, and scores of 20 or higher indicate moderate, severe, or very severe depression. The assessment time is around 20 minutes [25]. The HRSD, evaluated by the researcher to assess the degree of depression of patients with PSD, can give an objective and reflective outcome.

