##### Zung Self-Rating Depression Scale

Designed by Duke University psychiatrist William W. K. Zung [26], the SDS is intended to assess the level of depression of patients who have been diagnosed with depressive disorder. A short self-rated questionnaire, it consists of 30 items that rate the affective, psychological, and somatic symptoms closely related to depression. Each question is scored on a scale of 1 through 4 based on responses “*a little of the time,” “some of the time,” “good part of the time,” and “most of the time*.” Scores fall into four ranges as follows: 20–44 indicates normal, 45–59 indicates mildly depressed, 60–69 manifests moderately depressed, and 70 and above defines severely depressed [27]. The SDS, assessed by patients with PSD themselves, can present a subjective and direct outcome.

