### Sample size

According to the difference of HRSD scores between the two groups, the required sample size of each group will be carefully calculated by the data statistician. Based on our previous pilot study, the change in the SD of HRSD scores in the sham EA group is 5 points and that in the EA group is 13 points. If the HRSD score change in the EA group is 8.5 points higher than that in the sham EA group, it will be considered clinically significant. On the basis of a 5% false-positive error rate (α = 0.05, two-sided) and 80% power (β = 0.2), the sample size is estimated as follows:$$ {\displaystyle \begin{array}{l}n=\frac{{\left({Z}_{1-\alpha }+{Z}_{1-\beta}\right)}^2\times \left({\sigma}_1^2+{\sigma}_2^2\right)}{\delta^2}\\ {}\kern1.5em =\frac{{\left(1.96+1.28\right)}^2\times \left({5}^2+{13}^2\right)}{8.5^2}\approx 28.48\end{array}} $$

A sample size of at least 29 participants should be recruited in each group. Assuming about a 10% dropout rate, which has been verified in the pilot study, a total of 62 participants will be enrolled in the trial.

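### The inclusion criteria require DSM-5 insomnia and no depressive-disorder diagnosis, which contradicts the poststroke depression population the trial says it studies

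*Protocol article*

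**What the plan says.** Protocol article, Inclusion criteria: four conditions apply jointly. They are age 40 to 85; the diagnostic criteria of an acute ischemic stroke guideline "and the diagnostic criteria of insomnia according to the" DSM-5; depressive symptoms with onset after the stroke and an HRSD between 8 and 35; and consent. Insomnia is the only psychiatric diagnosis named.

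The rest of the article describes a depression trial. The Background gives the aim as to "comprehensively evaluate the efficacy and safety of EA treatment for PSD by comparing an EA group with a sham EA group". The Hypotheses section predicts that "Patients with PSD treated with EA will experience alleviation of their symptoms", with no mention of sleep. The primary outcome is change in HRSD. The Zung scale, a secondary outcome, is described as intended to "assess the level of depression of patients who have been diagnosed with depressive disorder".

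On the primary scale, the HRSD section states: "A score of 0–7 is considered to be normal". It describes the instrument as "probing mood, feelings of guilt, suicidal ideation, insomnia, agitation or retardation, anxiety, weight loss, and somatic symptoms". The Depression Scale of TCM also lists insomnia among its symptoms. Trial status says that participants are already being recruited.

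**The concern.** An eligibility rule defines the patients to whom the result applies, and no later analysis can recover patients whom the rule kept out. Here the one formal psychiatric diagnosis required at entry belongs to a different disorder from the one in the aim, hypotheses and conclusion. If the screening staff applied the sentence as printed, the trial answers a narrower question than the one it reports on, and a conclusion about PSD would reach beyond the patients studied.

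A secondary issue is interpretation of the outcome. If every participant must have insomnia, all of them enter with a symptom that the primary outcome and one secondary outcome both score. Part of an HRSD improvement could then reflect better sleep, to a greater extent than in an unselected PSD sample.

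**Working it through.** The point rests on text and no figure in the plan has to be reproduced. The check sets the sections side by side.

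1. **What the rule requires, read jointly.** Ischemic stroke, DSM-5 insomnia, depressive symptoms after the stroke, and HRSD 8 to 35. A depressive-disorder diagnosis appears in none of the criteria.

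2. **Whom the rule excludes.** A patient with poststroke depression who does not meet insomnia criteria fails the second condition. Such a patient belongs to the population named in the Background and Hypotheses. The article gives no reason for the restriction.

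3. **Whom the rule admits.** A patient with insomnia, some depressive symptoms since the stroke and an HRSD of 8. The article puts the upper end of normal at 7, so the entry floor is 8 − 7 = 1 point above it, on a scale that itself scores insomnia and somatic symptoms. A confirmed depressive disorder is not needed. A patient with insomnia and no depressive symptoms is not admitted, because the third condition still applies.

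4. **Whether another section resolves it.** Apart from the inclusion criterion, insomnia appears only as an adverse effect of antidepressants (Background) and as a symptom scored by the HRSD and the TCM scale. No sleep outcome is planned. Patient screening lists history, physical examination, laboratory tests and brain imaging, and none of these says which DSM-5 diagnosis is made. The account of the Zung scale presupposes diagnosed depressive disorder, which the entry rule does not require. Nothing explains or corrects the insomnia wording.

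5. **The sleep share of the outcome.** The HRSD section lists eight symptom areas: mood, guilt, suicidal ideation, insomnia, agitation or retardation, anxiety, weight loss and somatic symptoms. Insomnia is one of these eight, on an instrument rated along 24 dimensions with 3- or 5-point items. To bound the contribution of sleep to a group difference one would need the number of sleep items, their maximum scores and the expected change on them. The article gives none of these for the sleep items. The share therefore cannot be set against the planned difference (Sample size: "If the HRSD score change in the EA group is 8.5 points higher than that in the sham EA group"). Only the direction can be argued: selecting on insomnia may raise the share.

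**The case against.** The strongest reply is that this is a one-word slip. Aim, hypotheses and outcomes all point to depression and no sleep outcome is measured, which fits a drafting error at least as well as a deliberate restriction. That may be right, but the article does not show it. If it is a slip, the published eligibility rule is wrong and needs correcting; if it is not, the population differs from the stated question. Condensation for a journal would explain an omission. It does not explain naming a different disorder.

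A second reply is that depressive symptoms plus an HRSD range is a workable definition of PSD without a formal diagnosis. It is a possible design. However, this protocol invokes DSM-5 for a diagnosis and attaches it to insomnia, so the contradiction remains whichever definition was intended.

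Three stronger readings are tempting, and the documents support none of them:

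- *A reader might infer that the trial enrols people who are not depressed.* It does not. The next criterion requires depressive symptoms after the stroke and an HRSD above the normal range.
- *A reader might infer that a pure sleep effect could pass as an antidepressant effect.* Insomnia is one of several HRSD areas, and a sleep benefit would register to some degree in any PSD sample scored on this scale. The entry rule may enlarge that component, by an unknown amount. Both arms meet the same rule, so the randomised comparison stays valid. What suffers is generalisability and interpretation.
- *A reader might infer that all 62 planned participants are affected.* That assumes the sentence was applied as printed, which the documents do not show.

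**Conclusion.** The point stands as a contradiction between the eligibility text and the stated population. Its effect cannot be expressed as a number. If the sentence was applied as written, patients with PSD but no insomnia were excluded, those enrolled need no confirmed depressive disorder, and the result would not carry over to PSD in general. If another criterion was used in practice, the enrolled population may be the intended one and only the published rule is wrong.

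The textual contradiction is certain. The consequence for the enrolled sample is conditional on which criterion the screening staff used, and the article does not say. The point deserves correction now because the sentence is an operative rule, recruitment is under way, and the remedy is cheap.

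**What to change.** Reconcile the diagnostic criterion under Inclusion criteria with the PSD population in one of two ways:

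- If a depressive diagnosis was meant, replace insomnia with the specific DSM-5 depressive diagnosis intended, and keep the HRSD range of 8 to 35 as the severity criterion.
- If insomnia was meant, give the reason and restate the population in the title, aim, hypotheses and conclusion as stroke survivors with insomnia and depressive symptoms.

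In either case, check the screening records of those already enrolled and report which criterion was applied to them.

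The cost is a one-line amendment and a records check. If the insomnia criterion was really applied and a depressive diagnosis was intended, the diagnostic status of those enrolled would also have to be documented. The second option also means revising the wording of the aim and conclusion. Neither option changes the randomisation or the sample size calculation as written.

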#### Exclusion criteria

Patients in a state of coma or with severe disturbance of consciousness, aphasia, agnosia, or deafness that subsequently affects expression and communicationPatients with complications of severe heart failure, respiratory failure, renal insufficiency, other severe diseases in acute stage, or other neurological/musculoskeletal disorders that affect functional rehabilitationPatients who are afraid of EA treatment or are reluctant to accept it

#### Dropout criteria

Patients who accept other treatments except EA for PSD during observation periodPatients who fail to or are unwilling to finish the EA treatment schedule

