### Interventions

All the eligible participants will be randomized into one of two groups: the EA group or the sham EA group. The EA treatment, consisting of 12 sessions across 4 weeks with 3 sessions each week, will be performed by experienced acupuncturists to ensure identical acupuncture treatment according to standard operating procedures. The participants in both groups will receive treatment by acupuncturists at the same acupoints as follows: Baihui (DU20), Sishencong (EX-HN1), Ganshu (BL18), Sanyinjiao (SP6), and Taichong (LR3), all of which are the most frequently used acupoints for treating PSD according to previous research. The needle retention time in both groups is 30 minutes. In addition to EA treatment, the participants will receive basic Western medical therapy for stroke (Table 1).

**Table 1 Tab1:** Intervention details of both groups

	EA group	Sham EA group
Acupoints	DU20, EX-HN1 BL18, SP6, LR3	DU20, EX-HN1 BL18, SP6, LR3
Needle penetration	DU20, EX-HN1: 10 mm BL18, SP6, LR3: 15 mm	No needle penetration
Needle stimulation	De-qi sensation	No de-qi sensation
Electrostimulation	Current frequency: 2/100 Hz	No electrostimulation
Needle retention time	30 minutes	30 minutes
Treatment tools	Stainless steel needles and a PG-306 electroacupuncture device	A Park Sham Device with a PG-306 electric pulse generator with a cut wire inside
Treatment frequency and duration	Three sessions per week, 4 weeks	Three sessions per week, 4 weeks

*Abbreviations: BL18* Ganshu, *DU20* Baihui, *EA*, Electroacupuncture, *EX-HN1* Sishencong, *LR3* Taichong, *SP6* Sanyinjiao

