#### Primary outcome

The changes in HRSD scores between baseline, 2 weeks after EA treatment onset, 4 weeks after treatment onset, and at 8-week follow-up will be set as the primary outcome of the clinical study.

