### Statistical analysis

An independent statistician will use IBM SPSS Statistics 24.0 software to conduct the whole data analysis. According to the intention-to-treat (ITT) principle, both ITT and per-protocol (PP) analyses will be performed. Any participant who receives treatment more than nine times during the study will be enrolled in the PP analysis. In terms of ITT analysis of secondary outcomes, the last observation carried forward rule will be used as the strategy in management of missing data. For the primary outcome, the maximum likelihood estimation method will be used.

All continuous variables will be presented as mean ± SD, and categorical variables will be presented as number (percent). The statistical significance level is considered to be 0.05 (two-sided) with 95% CIs. The homogeneity of the baseline characteristics between the two groups is designed to be tested by the two-sample *t* test for quantitative data and the chi-square test for qualitative data. If there is a possibility of covariance, analysis of covariance (ANCOVA) will be used for adjustment of baseline characteristics. To compare variables between the two groups, the parametric two-sample *t* test for normally distributed data and the nonparametric Mann-Whitney *U* test for nonnormally distributed data will be used. Repeated-measures ANCOVA will be applied to analyze different time point assessments between groups and interaction between groups and observed time. Differences within groups will be assessed with the paired *t* test (parametric method) and the Wilcoxon signed-rank test (nonparametric method).

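### The dropout criteria do not separate stopping or adding treatment from leaving the study, which sits badly with ITT, and they conflict with the per-protocol rule

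*Protocol article*

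**What the plan says.** All references are to the protocol article.

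- **Dropout criteria.** The two list items, run together in the extracted text, read: "Patients who accept other treatments except EA for PSD during observation periodPatients who fail to or are unwilling to finish the EA treatment schedule". They apply to both arms. The section does not say what follows from being a dropout.
- **Interventions.** The full schedule is described as "consisting of 12 sessions across 4 weeks with 3 sessions each week".
- **Primary outcome.** HRSD change is followed past the end of treatment: the assessments at "2 weeks after EA treatment onset, 4 weeks after treatment onset, and at 8-week follow-up will be set as the primary outcome".
- **Sample size.** At least 29 per group are required, about 10% dropout is assumed, and 62 are to be enrolled.
- **Statistical analysis, analysis sets.** "According to the intention-to-treat (ITT) principle, both ITT and per-protocol (PP) analyses will be performed". For the second set: "Any participant who receives treatment more than nine times during the study will be enrolled in the PP analysis". No condition on other PSD treatment is attached.
- **Statistical analysis, missing data.** For HRSD: "For the primary outcome, the maximum likelihood estimation method will be used". For the secondary outcomes under ITT: "the last observation carried forward rule will be used as the strategy in management of missing data".

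**The concern.** An ITT comparison needs outcomes from everyone randomized, whatever treatment they went on to receive. Taking another depression treatment and missing sessions are things that happen to a patient's treatment. They do not in themselves prevent anyone from rating that patient's HRSD. By calling them dropout, with no separate category for withdrawal from the study, the article invites site staff to stop assessing these patients, or analysts to set their later scores aside.

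If that happens, the loss could be related to outcome. Besides the study treatment, the Interventions section provides only basic medical therapy for stroke, so a patient whose depression does not improve has a reason to accept something else. Unblinded acupuncturists could also influence who finishes.

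The second problem needs no assumption about conduct. The Dropout criteria and the PP rule classify some of the same patients in opposite ways, so two analysts could build different PP sets from the same text. One of those sets would contain patients on other depression treatment. The Discussion criticizes combined interventions because they obscure the specific effect of acupuncture.

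**Working it through.** **1. The plan's own figures.** With the printed values, n = (1.96 + 1.28)² × (5² + 13²) / 8.5² = 10.4976 × 194 / 72.25 = 28.19. The article prints 28.48; both round up to 29 per group, or 58 in total. Enrolling 62 leaves 4 spare, 4/62 = 6.5%. So the article expects some patients to be lost, but it does not say that these are the patients meeting the Dropout criteria.

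**2. Is this a power problem?** With 31 per group and 10% lost, 27.9 per group remain. Under the protocol's SDs and the 8.5-point difference, power is 89.7% (86.0% at 20% loss, 81.1% at 30%). All exceed the stated 80%. The issue is possible bias.

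**3. Overlap of the two rules.** Not finishing means fewer than 12 sessions; the PP rule requires more than 9.

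| Patient | Dropout criteria | PP rule |
|---|---|---|
| 9 or fewer sessions | dropout | out |
| 10 or 11 sessions | dropout | in |
| 12 sessions, no other PSD treatment | not a dropout | in |
| 10 to 12 sessions, other PSD treatment in the observation period | dropout | in |

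The second and fourth rows conflict.

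**4. How far could informative loss move the contrast?** The article gives no loss rates by arm and no reasons for loss, so everything here is assumption. Score improvement as positive, take the true difference as 8.5 and changes as normal with SD 13 (EA) and 5 (sham), and analyse observed cases only.

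*Worst case: the lowest-improving fraction p of an arm is lost.* The mean of those remaining rises by SD × φ(z_p)/(1 − p). At p = 0.10 the factor is 0.1755/0.90 = 0.195.

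- Shift in sham: 5 × 0.195 = 0.97.
- Shift in EA: 13 × 0.195 = 2.53.
- Sham only: 8.5 − 0.97 = 7.53, about 7.5.
- Both arms: 8.5 + 2.53 − 0.97 = 10.06, about 10.1.

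The sign changes with the assumption about who leaves, because the EA SD is 2.6 times the sham SD.

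*Milder selection: 75% to 100% of those lost come from the lower half of their arm (simulated).*

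| Loss EA / sham | Observed difference |
|---|---|
| 10% / 10% | 8.9 to 9.2 |
| 5% / 15% | 8.4 to 8.3 |
| 10% / 20% | 8.6 to 8.7 |
| 15% / 5% | 9.3 to 10.1 |

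**5. What the planned missing-data methods do.** These figures do not describe the planned primary analysis. Maximum likelihood uses the visits that were observed and is valid if, given those visits, the chance of being missing does not depend on the unseen score. That may fail when a patient worsens between visits and starts another treatment before being rated again. Last observation carried forward holds the last score fixed, so it can be biased even when data are missing at random.

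**The case against.** The strongest reply is that the article never says assessment ends at dropout, that scores are discarded, or that anyone leaves the ITT set. It states the ITT principle and plans maximum likelihood for HRSD. It is also a condensed account: rules for visits after treatment stops commonly sit in the full protocol, and their absence here is no finding. A PP threshold below full attendance is ordinary, the article does not say that dropouts leave the PP set, and the PP analysis does not alter the ITT comparison.

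Most of this stands, and it limits the claim. A reader might infer that HRSD data will be lost selectively from non-responders, chiefly in the sham arm, and that the planned 8.5-point difference will shrink. The documents do not support that. The criteria apply to both arms, no reasons or rates by arm are given, and sessions can be missed for causes unrelated to response. Shrinkage arises when sham alone loses its poorest improvers; the same formula at 10% in both arms enlarges the difference.

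What the reply does not remove is what the article states. It labels two events after randomization as dropout without separating them from leaving the study, and its Dropout criteria and PP rule disagree about identifiable patients. Neither point rests on silence alone.

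**Conclusion.** The point holds as a risk and as a contradiction, and it should be fixed. The contradiction is certain: patients with 10 or 11 sessions, and those with more than nine sessions who took other PSD treatment, are dropouts under one section and per-protocol under another.

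The threat to the ITT analysis is conditional on HRSD not being collected or used after these events, and on that loss depending on outcome in a way the observed visits do not explain. Its direction and size are undetermined. The range of about 7.5 to 10.1 around a true 8.5 illustrates two worst-case patterns at 10% loss with observed cases only. It is neither a forecast nor a bound, and maximum likelihood could recover part of any such bias. The secondary outcomes are less protected.

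**What to change.** 1. Replace the Dropout criteria with a rule that records these events, with type and date, as treatment discontinuation or as other PSD treatment. Keep study dropout for patients who withdraw consent to assessment.
2. State that HRSD and all secondary scales continue to be collected at the scheduled visits through follow-up unless that consent is withdrawn, and that these data enter the ITT analysis.
3. Reconcile the PP definition with the revised criteria. Say how an unfinished schedule relates to the session threshold, and add a condition on other PSD treatment. Which threshold to use is for the trial team.

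The cost is protocol wording and continued follow-up at visits already in the schedule. Some scores will be measured after other treatment has begun, and the PP set may be slightly smaller. Trial status reports that recruitment is under way, so the change is best made promptly: assessments that are not made cannot be recovered at analysis.
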